## Abstract

Early implementation of interventions at a young age fosters behaviour changes and helps to adopt behaviours that promote health. Digital technologies may help to promote the hand hygiene behaviour of children. However, there is a lack of digital feedback interventions focusing on the hand hygiene behaviour of preschool children in childhood education and care settings. This study protocol aims to describe a study that evaluates the effectiveness of a gamified live feedback intervention and explores underlying behavioural theories in achieving better hand hygiene behaviour of preschool children in early childhood education and care settings. This study will be a four-arm cluster randomized controlled trial with three phases and a twelve-month follow-up by country stratification. The sample size is 106 children of which one cluster will have a minimum number of 40 children. During the baseline phase, all groups will have automated monitoring systems installed. In the intervention phase, the control group will have no screen activity. The intervention groups will have feedback displays during the handwashing activity. Intervention A will receive instructions, and intervention B and C groups will receive instructions and a reward. In the post-intervention phase, all the groups will have no screen activity except intervention C which will receive instructions from the screen but no reward. The outcome measures will be hand hygiene behaviour, self-efficacy, and intrinsic motivation. Outcome measures will be collected at baseline, intervention, and post-intervention phases and a 12-month follow-up. The data will be analysed with quantitative and qualitative methods. The findings of the planned study will provide whether this gamified live feedback intervention can be recommended to be used in educational settings to improve the hand hygiene behaviour of preschool children to promote health.

The trial is registered with ClinicalTrials.gov (registration number NCT05395988
https://clinicaltrials.gov/ct2/show/NCT05395988?term=NCT05395988&draw=2&rank=1).

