### Sample size

The sample size is calculated based on the significant effects found during the pre-study. In the pre-study, 10,000 handwashing events were recorded over a period of 42 days in a treatment group (n = 82 children in two clusters) and a control group (n = 53 children in two clusters). Using Cohen’s power analysis with f^2^ = 0,35 (large effect size) and power level of 0.8 and 2 predictors and a probability level of 0.05 leads to n = 31. However, since randomization is on a cluster level, the n must be increased. With the ICC from the pre-study of 0.062, and estimated cluster size (size of each kindergarten) of 40 children, we calculate the design effect:

D=1+(m−1)*ICC=1+(40−1)*0.062=3.418

Thus, we need to increase the sample size by 3.418 compared to individual randomization, due to cluster randomization leading to 106 participants (n = 31 * 4.418 = 106). With the assumption of a cluster size of 40 children per kindergarten, this leads to three kindergartens that need to participate in the study. Each kindergarten represents one cluster and gets assigned to be the control, the intervention A, B, and C groups. Two intervention groups will be covered by one cluster.

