### Randomization

The cluster randomization will be at the kindergarten level. Kindergartens will be randomly assigned to control or intervention groups by two researchers that are not members of the research team and are stratified by country. One kindergarten serves as one cluster. Simple randomization will be used which will be drawing lots, where each cluster will be assigned a number in a piece of paper. The parents will enrol their children for participation in the study within the time set through the website link provided and email.

No information will be given regarding the allocation. Allocation will be about four weeks before the start of the baseline phase and will be conducted by the two non-member researchers. They will generate the allocation sequence, enroll the participants, and assign them to control or intervention groups. There will be complete concealment of the allocation from the members of the research team and the participants, to exclude the possibility of predicting the next allocation [33].

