This study will use multiple measurements such as a monitoring system, survey, interview, and observation to assess hand hygiene behaviour, self-efficacy, and motivation. This will provide versatile data to support the effectiveness of the intervention. It will also provide information if self-efficacy and motivation play important roles in attaining hand hygiene behaviour. Another is to provide further evidence if preschool children’s self-efficacy is a significant variable in determining the effectiveness of the intervention and obtaining hand hygiene behaviour. In this study, hand hygiene self-efficacy for preschool children will be developed and evaluated which up to these days none have been developed. This study will also measure the sick leave days of the children and kindergarten staff which could give information if using the intervention is effective in reducing the number of sick leave days. Hand hygiene interventions in educational settings showed to decrease the spread of infectious illnesses [3,7] and reduce absenteeism [3]. This study will use a cluster randomized controlled design which includes larger participants and a long follow-up period. Systems will be installed in all the groups which can provide concrete data on the handwashing activities. Another strength of this study will be assessing the children’s self-reports as there are few interventional studies that measured this. Evaluating the effectiveness of the gamified live feedback intervention will enable the research team to determine if this kind of approach is worth implementing to improve handwashing practices in various settings i.e., clinical, and educational settings.

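### At the three kindergartens that the sample-size section asks for, no arm is replicated, so the stated power of 0.8 is not delivered for comparisons between arms

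*Protocol article*

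**What the plan says.** Under Sample size, the protocol article takes Cohen's f² = 0.35, a "power level of 0.8", 2 predictors and "a probability level of 0.05 leads to n = 31". It then applies an ICC of 0.062 from the pre-study and a cluster size of 40, which gives a design effect of 3.418 and 106 children. At 40 children each, "this leads to three kindergartens that need to participate in the study". On allocation: "Each kindergarten represents one cluster and gets assigned to be the control, the intervention A, B, and C groups". The next sentence adds that one cluster will serve two of the intervention groups.

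Trial design describes four arms and makes one kindergarten one cluster. Under Randomization, "The cluster randomization will be at the kindergarten level", stratified by country. Data analyses plans a linear fixed-effect panel regression of soaping time, comparing the four groups in the baseline, intervention and post-intervention phases. The Abstract says that the findings will show "whether this gamified live feedback intervention can be recommended to be used in educational settings".

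**The concern.** A design effect corrects the variance of a mean for clustering when the ICC is taken as known. It does not supply the repeated clusters within each arm from which variation between kindergartens has to be estimated. The section carries a power figure from a calculation on independent children over to a design with at most one kindergarten per arm.

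A contrast between arms in different kindergartens is then a contrast between single kindergartens. More children or more recorded handwashing events make each kindergarten's own figure more precise, but add no information on how much kindergartens differ in their course over time. A reader would take the result as that of a cluster trial with 80% power and could act on the recommendation that the Abstract has in view.

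**Working it through.** **1. The plan's own figures.** Inputs from Sample size: f² = 0.35, 2 predictors, alpha 0.05, ICC 0.062, m = 40.

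- Noncentral F with df1 = 2, df2 = n − 3 and noncentrality 0.35 × n: n = 30 gives power 0.789 and n = 31 gives 0.804. So n = 31 reproduces, with df2 = 31 − 3 = 28.
- Design effect: 1 + 39 × 0.062 = 3.418.
- 31 × 3.418 = 105.96, so 106 reproduces. The printed multiplier of 4.418 would give 136.96 and is a slip.
- 106 / 40 = 2.65, rounded up to three kindergartens.

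**2. Degrees of freedom at the randomised level.** Residual df = kindergartens − conditions. If the two arms sharing a kindergarten count as one condition, 3 − 3 = 0. For four arms, 3 − 4 = −1. No between-kindergarten test of arms exists in either case.

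**3. Smallest randomisation p-value.** Three kindergartens can be drawn in 3! = 6 orders, so the minimum is 1/6 = 0.17 if the pair of arms sharing a kindergarten is fixed in advance. If that pair is also drawn, there are 3 possible pairs among A, B and C, hence 3 × 6 = 18 allocations and a minimum of 1/18 = 0.056. Both exceed 0.05. Stratifying the draw by country can only reduce the number of possible allocations.

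**4. Treating children as independent.** For an unadjusted comparison of two kindergartens, 40 against 40, at ICC 0.062, the true variance is about 3.418 times the naive one. The type I error at nominal 0.05 is about 2 × [1 − Φ(1.96 / √3.418)] = 2 × [1 − Φ(1.06)] = 0.29.

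**5. What more kindergartens would give.** Cluster-level F test for four arms: df1 = 3, df2 = C − 4, noncentrality = C × 40 × 0.35 / 3.418, with the plan's f², ICC and cluster size kept.

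| Kindergartens (C) | Residual df | Noncentrality | Power |
|---|---|---|---|
| 3 | −1 | – | no test |
| 4 | 0 | – | no test |
| 5 | 1 | 20.48 | 0.15 |
| 6 | 2 | 24.58 | 0.37 |
| 7 | 3 | 28.67 | 0.64 |
| 8 | 4 | 32.77 | 0.83 |

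With eight kindergartens and one df spent on country, power is 0.69.

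**The case against.** **Three may be only a minimum.** Study setting and Eligibility criteria open the trial to kindergartens around two cities, nothing caps enrolment, and the cluster flowchart (Fig 8) is not shown. This stands as far as it goes: a reader might infer that exactly three kindergartens will take part, and the article does not say so. But no visible text plans more, and the section presents three as what power 0.8 requires. That claim fails whatever is recruited. If three were meant per country (an assumption, six in all), power after a country term would be about 0.16 for four arms (1 df) and 0.49 for three conditions (2 df).

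**The baseline phase is in the design.** Every kindergarten has a three-week monitored baseline, and kindergarten fixed effects would remove stable differences. This stands too. It would be too strong to say that an arm effect cannot be told from any difference between kindergartens, or to use the ICC of 0.062 as the noise in a change from baseline; the article gives no ICC for change. What remains is change peculiar to one kindergarten, such as an outbreak or a new staff routine. With one kindergarten per arm, its variance cannot be estimated.

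**Not every hypothesis compares arms.** H3b and H3c set an arm against its own baseline, so a lack of between-arm degrees of freedom does not directly address them. A reader might infer that all of H1 to H4 fall; that is not shown. The contrast between the two arms sharing a kindergarten is likewise not a between-kindergarten contrast and raises a different question.

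**The strengths paragraph.** The Discussion says "This study will use a cluster randomized controlled design which includes larger participants and a long follow-up period". The pre-study had 82 + 53 = 135 children in four clusters, so one might read this as contradicted. The sentence names no comparator, and the point does not rest on it.

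**Conclusion.** The point holds for between-arm comparisons at the stated number of kindergartens. The arithmetic to 106 children and three kindergartens is sound apart from the misprinted multiplier. The error lies in reading the result as power 0.8 for a four-arm cluster comparison. The calculation itself did not use zero degrees of freedom: it used 28, and those do not carry over to the randomised level.

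The degrees-of-freedom result needs only the article's counts of kindergartens and arms. The 0.29 applies to an unadjusted analysis that ignores clustering, not to the planned panel model. The power values for five to eight kindergartens assume that f² = 0.35 and the ICC carry over to the four-arm comparison, with 40 children in each kindergarten. The size of the remaining confounding with kindergarten-specific change is unknown.

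**What to change.** In Sample size, withdraw the 0.8 for between-arm contrasts at three kindergartens. State that no randomisation-based test at 0.05 is possible there, giving the smallest attainable p-value and saying whether the pair of arms sharing a kindergarten is fixed in advance or drawn. State that the between-arm contrasts in the hypotheses are estimates for these kindergartens and not confirmatory tests, and limit the Abstract's closing conclusion to match.

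If more kindergartens are already committed, give their number and recompute power with residual df = kindergartens − arms − any stratum terms.

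The cost is rewording in two places, with a less favourable power statement and a weaker conclusion. No further recruitment is asked for.

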**Fig 1 pone.0280686.g001:**
[figure not shown]
Schedule of enrolment, intervention, and assessments.

This study will be a four-arm cluster randomized controlled trial study with three phases and a twelve-month follow-up by country stratification. This study will evaluate the effectiveness of the gamified live feedback intervention on children’s handwashing behaviour, self-efficacy, and motivation in three different phases: the baseline, intervention, and post-intervention phases. In Finland, there will be a twelve-month follow-up after the baseline phase. This study will consist of four groups, the control group, and three different intervention groups. All the groups will have automated monitoring systems installed before the start of the baseline phase and will be available in all phases. The system will be de-installed after the post-intervention phase.

During the baseline phase, all the groups will have no screen activity. During the intervention phase, the control group will have no screen activity. The intervention A group will have a screen display providing handwashing instructions but no reward, and the intervention B and C groups will receive handwashing instructions and rewards from the screen display. During the post-intervention phase, all the groups will have no screen activity except the intervention C group which will receive handwashing instructions but no reward (Fig 2).

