**Fig 2 pone.0280686.g002:**
[figure not shown]
The design and data collection of the study.

The design of this study is cluster randomized controlled, where one kindergarten serves as one cluster. Clustering will be used since the hand hygiene intervention is designed to be installed in certain areas to be used in groups. Kindergartens will be assigned as clusters rather than individuals to minimize the potential contamination among the groups, and to more accurately follow the process that will be taken at scale [33,34].

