### Study setting

This study will be conducted in kindergartens of different locations around Turku, Finland and Bamberg, Germany. In Germany and in Finland, kindergartens are under the supervision of Early Childhood Education and Care (ECEC) [36]. It is a part of Finnish and German education systems which support the children’s development and focus on learning through play. It is an essential stage on the child’s path of growing and learning. ECEC is a systematic and goal-oriented entity that includes upbringing, education, and care, specifically emphasizing pedagogy aiming to promote and support holistic growth, development, health, and wellbeing (Act on Early Childhood and Care). Groups of children in the kindergartens may be formed in various ways, considering the children’s ages or needs for support. Distribution on staffing and maximum group sizes are considered in forming the groups of children. The kindergarten staff are composed of preschool teachers and assistants who are responsible for the daily activities of the children [36–39].

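### Lots are drawn only between kindergartens, yet two intervention arms share one kindergarten, and no random allocation between those two arms is described

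*Protocol article*

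**What the plan says.** On allocation, the Randomization section of the protocol article is explicit: "The cluster randomization will be at the kindergarten level", and "One kindergarten serves as one cluster". The method is also given: "Simple randomization will be used which will be drawing lots, where each cluster will be assigned a number in a piece of paper". Two researchers from outside the team carry it out, about four weeks before baseline, with stratification by country.

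On arms and clusters, the Trial design section says: "This study will consist of four groups, the control group, and three different intervention groups". The Sample size section concludes that "this leads to three kindergartens that need to participate in the study", repeats that each kindergarten is one cluster, and closes with: "Two intervention groups will be covered by one cluster". It does not say which two arms share.

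The Trial design section also gives the reason for allocating whole kindergartens: "Kindergartens will be assigned as clusters rather than individuals to minimize the potential contamination among the groups".

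On the setting, the article says: "Groups of children in the kindergartens may be formed in various ways, considering the children’s ages or needs for support". This describes early childhood settings in general. It is not a rule for dividing arms.

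**The concern.** Four arms in three kindergartens means that one building holds two arms. The only random step described operates on whole buildings, so it stops at the door of the shared one. Someone must still decide which washbasins get which screen content, and the article gives that decision no unit and no chance mechanism.

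Planned hypotheses depend on the result. If A is one of the sharing arms, the comparison of A with B or C in H1 and H4a is affected. If B and C share, the comparison of B with C in H2 and H4b is affected. Either contrast would be presented as part of a cluster randomised trial although the described procedure does not randomise it.

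This is a separate matter from children seeing the other arm's display. Selective placement of screens, or a division that coincides with some characteristic of the children, would distort the contrast even if no child ever used the other arm's sink.

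**Working it through.** **1. Where three kindergartens come from.** Inputs from the Sample size section: f² = 0.35, power 0.80, 2 predictors, alpha 0.05, ICC 0.062, cluster size 40.

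- Overall F test in regression (noncentrality f² × N; 2 and N − 3 degrees of freedom): power is 0.789 at N = 30 and 0.804 at N = 31. The plan's n = 31 is reproduced.
- Design effect: 1 + 39 × 0.062 = 3.418, as printed.
- 31 × 3.418 = 105.96, rounded up to 106, as printed. The multiplier 4.418 shown in the text would give 136.96, so it is read here as a misprint for 3.418.
- 106 / 40 = 2.65, rounded up to 3 kindergartens, as printed.

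So the shared kindergarten follows directly from the plan's own calculation.

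**2. What the stated lot can decide.**

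| Decision | Settled by one lot per kindergarten? |
|---|---|
| Which kindergarten is control | Yes |
| Which kindergarten holds two arms | Yes |
| Which washbasins, rooms or children in that kindergarten get which of the two arms | No |

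**3. Whether a division is needed for every possible pair.** A differs from B and C in the intervention phase, because only B and C have the reward. B and C have the same planned content in that phase, but afterwards C keeps an instruction screen and B has none (Trial design). So every pair needs a division inside the building, at the latest by the post-intervention phase.

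**4. How large an imbalance could be.** The article does not state the rule for dividing, so only a range can be given, using age as the example.

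- Mixed-age groups, or a division by sink within shared rooms: age gap about 0.
- Assumed worst case: ages spread evenly over the eligible range of 2.5 to 6 years and a complete younger/older split. The midpoint is 4.25. The halves average (2.5 + 4.25)/2 = 3.375 and (4.25 + 6)/2 = 5.125. The gap is 1.75 years.

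**5. How much information the contrast carries.** With an even split (assumption), each of the two arms has about 20 children. Using the plan's ICC, 20 / (1 + 19 × 0.062) = 20 / 2.178 = 9.2 effective children, against 40 / 3.418 = 11.7 for an arm with its own kindergarten. If a second lot were drawn between 2, 4 or 6 units divided equally, there would be 2, 6 or 20 possible allocations, so the smallest one-sided randomisation p-value would be 1/2, 1/6 or 1/20. The number of washrooms or child groups per kindergarten is not given.

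**The case against.** Four objections deserve an answer.

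*The article is condensed, and the draw may exist elsewhere.* The two outside researchers are said to assign participants to groups, and the randomisation flowchart is not visible in the text at hand. That is a fair reason not to say the division will certainly be unrandomised. It does not clear the point. The article states the unit and the method positively, both are whole kindergartens, and neither fits two arms in one kindergarten. This is a conflict between two sections rather than an omitted detail.

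*Nothing says the arms follow child groups.* Correct. A reader might infer from the Study setting section that the two arms will be a younger and an older group. That section says only how groups may be formed in such settings, and installation at each washbasin would equally allow division by sink or room. Confounding by age is a possibility, not a stated feature of the design.

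*The plan already handles stable differences.* In part. There are three weeks of sensor baseline, and soaping time is analysed with a fixed-effect panel model. If the panel unit is a sink or child group, stable differences drop out and only differences in response remain. If the unit is the kindergarten, the fixed effect is common to both arms and removes nothing between them. The unit is not stated. Child interviews and observations also have a baseline, and child age is collected, though the Data analyses section does not name it as a covariate. The parent survey (last intervention week only) and the staff interview (last intervention week and first post-intervention week) have no baseline, and the sensor data are not linked to individual children.

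*A second lot cures little.* It removes selective placement. If the only units are two groups of different ages, it decides which arm receives the older group and leaves the gap. This limits the remedy. It is also true that every other arm contrast is confounded with kindergarten when only three take part, so this contrast is not uniquely weak.

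**Conclusion.** The point stands in this form: the Randomization and Sample size sections cannot both be followed as written without leaving one arm contrast unrandomised. No random allocation between the two arms in the shared kindergarten is described, and one lot per kindergarten cannot supply it. The contrast is open to selection and to confounding by however the kindergarten is divided.

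The size is unknown. In age terms it runs from about 0 to 1.75 years, and the upper end assumes evenly spread ages and complete segregation. A reader might turn this into a bias of 0.18 to 0.53 SD by assuming outcomes change by 0.1 to 0.3 SD per year of age (1.75 × 0.1 and 1.75 × 0.3). The documents give no such gradient, and that interval starts from the worst-case split. On the same assumed gradients the range would begin near 0, and part of any stable difference may be removed by the baseline data. The SD figures should not be quoted as an expected bias.

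The affected hypotheses depend on which pair shares, which the article leaves open.

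**What to change.** Reconcile the Sample size and Randomization sections as follows.

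- State which two arms share a kindergarten.
- Name the allocation unit inside it: washrooms, washbasins or child groups.
- Have the same two outside researchers draw a second, concealed lot between those units, preferably units of similar age mix, and record that age mix.
- Compare these two arms on change from baseline where a baseline exists, with child age as a covariate for child-level outcomes. State the panel unit of the soaping-time model so that it lies below the kindergarten for this contrast.
- Report the contrast as a within-kindergarten, group-level comparison of very few units, separately from those allocated by kindergarten. Note that parent and staff measures cannot be adjusted for baseline.

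The cost is one extra draw and a note of group ages. The kindergarten's preferred placement of screens may not be followed, and the contrast will look weaker on paper than it does now.

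The alternative is one whole kindergarten per arm: at least 4 kindergartens, or 4 × 40 = 160 children instead of 3 × 40 = 120. That removes the internal division and agrees with the stated aim of limiting contamination, but with one kindergarten per arm this contrast would then also be confounded with kindergarten.
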